For the evaluation, a cumulative value was formed for each scale wherein the ticked answers were added, whereby some items had to be reversed beforehand. The cumulative value starts with 1 as the lowest level of the construct and, depending on the number of items, ranges from 21 (3 items) to 28 (4 items; the highest level). The ITU Scale is an exception because, to evaluate this scale, we measure the distance from the right end point (full rejection) to the answer at the intersection of the line. The distance in millimeters was determined and added to all 3 items (A, B, and C). The maximum scale value achievable is 300. Total scale values are converted into standard values (stanins and percentage rankings) using a standard table (Table 3). Thus, a statement of the relative proportion of participants who achieved the same or lower values is feasible. Therefore, a percentage ranking between 40 and 60 represents the absolute average [46].

The System Usability Scale (SUS) assesses the usability of a system that is subjectively perceived by the user and is demonstrably technology-independent, that is, SUS can be used for a wide range of systems and technologies [47,48]. The 10 items of the SUS are divided into 5 positive and 5 negative statements, each of which is represented on a Likert scale from 0 to 5. The responses are used to derive the SUS item score, which is then converted into the overall SUS score (from 0 to 100). To calculate the overall SUS score, the raw value minus 1 was calculated for all odd items in the first step, whereas the raw value of 5 was subtracted from the even items. For example, if item 1 had a raw score of 4, the score would be 3 (obtained as 4 − 1). For item 2, if the raw score was 2, then the score was 3 (derived as 5 − 2). Next, the newly calculated scores were summed and multiplied by 2.5 to obtain the overall SUS score [49]. Systems are considered fit if they achieve a benchmark of 68 [48,49]. The score is not to be understood as a linear percentage but moves on a percentile and requires a corresponding interpretation [48-50]. In a preliminary study, an adjective scale was developed for a more comprehensive classification of the SUS scores [50] (Table 4).

**Table 2 table2:** Measurement times Technology Usage Inventory (TUI).

Measure times	TUI version^a^	Scale
T1: Adoption—before the technology was introduced	TUI original questionnaire (pre-post version)	NEU^b^ and ANG^c^

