T2: Task—testing the technology	TUI II parallel questionnaire (complete version)	NEU, ANG, INT^d^, BEN^e^, NÜT^f^, SKE^g^, ZUG^h^, and ITU^i^
T3: Behavior—end of technology testing	TUI II parallel questionnaire (complete version)	NEU, ANG, INT, BEN, NÜT, SKE, ZUG, and ITU

^a^Designation according to the official TUI manual (Kothgassner et al [45]).

^b^NEU: curiosity.

^c^ANG: fear of using a technology.

^d^INT: interest.

^e^BEN: user friendliness.

^f^NÜT: usefulness.

^g^SKE: skepticism.

^h^ZUG: accessibility.

^i^ITU: intention to use.

**Table 3 table3:** Percentage ranks and stanins.

Percentile rank	Stanine	Percentage (%)
0-4^a^	1	4
>4-11^a^	2	7
>11-23^b^	3	12
>23-40^b^	4	17
>40-60^c^	5	20
>60-77^d^	6	17
>77-89^d^	7	12
>89-96^e^	8	7
>96-100^e^	9	4

^a^Strongly below average.

^b^Slightly below average.

^c^Average.

^d^Slightly above average.

^e^Strongly above average.

The measurement time T1 of the SUS was parallel to the measurement time T3 of the TUI at the end of the trial.

Statistical advice for study planning was obtained from the Institute for Medical Epidemiology, Biometry and Computer Science. As this involved an explorative approach, calculation of the number of cases was unnecessary and was therefore derived from investigations by Faulkner [51], who examined the number of problem identifications in relation to their dependence on the number of subjects. With a sample size of 5 subjects, an average of 85% and at least 55% of 100 problems could be identified, with a very high SD of 9.3. Faulkner [51] indicates that at least 50 subjects are needed to identify an average of 100% of the 100 given problems. As the study duration and the intensity of data acquisition are limited by the human resources available for the project and the project duration, this study used a sample size of up to 45 nurses, which means that 15 nurses are evaluated per ward and per clinical unit.

**Table 4 table4:** Adjective scale of the System Usability Scale (SUS) score (Bangor et al [50]).

Acceptance range and SUS score		Adjective scale

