## Results

Data collection would begin in the summer of 2023, and the initial results are expected in the winter of 2023. This study will evaluate the implementation of DFree to support nurses in reducing their workload pertaining to continence care. A change in ITU (TUI Scale) is expected. To investigate the possible causes for the measured change, 7 additional characteristics—curiosity (NEU), anxiety about technology, interest (INT), usability (BEN), usefulness (NÜT), skepticism (SKE), and accessibility (ZUG)—will be evaluated 3 times. Furthermore, this study will generate structured feedback that can support developers in further improving DAT DFree. Consequently, a reduction in the number of unsuccessful toilet visits or uncontrolled micturition events while wearing DFree will be recorded and documented by nurses through numerical counting. This will show whether the use of DFree is a practical and advantageous measure for mitigating the nurses’ workload in the context of continence care. As nurses are often poorly equipped to respond to such DAT implementation, the results should serve as a guideline for further improvement of DFree. The combination of qualitative and quantitative instruments addresses the additional aspects that nursing staff would have in mind but will not be assessed using only a quantitative instrument (TUI). Additionally, a change in the perceived usability of the DFree app among nurses is expected.

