## Discussion

This pilot study will implement DFree in continence care, give nurses an opportunity to try DFree in real-world practice, and enable the possibility of further cocreative development. The study design enables a novel practical testing of a DAT together with an opportunity for cocreative improvement through direct user feedback. This was the first pilot study to evaluate the use of the DFree ultrasound sensor in an inpatient care setting. This study is the first of its kind and is highly relevant, especially in the context of the barriers to the practical implementation of measures for the digital transformation of health care. The results and experiences from this study facilitate an effect assessment for subsequent studies and serve as a basis for methodological and organizational modifications. Therefore, it is important to evaluate quantitative data in terms of technically meaningful measures. Nonetheless, the study has some limitations, such as the small sample size, diversity of bladder dysfunctions (urinary incontinence and urinary retention), and the impossibility of extrapolating quantitative results to other populations. Additionally, no control group has been included in this study. Nevertheless, this pilot study provides the first assessment of nurses’ ITU a DAT, the DFree ultrasound sensor, and provides initial data for further controlled clinical studies. The strengths of this study include the triangulation of quantitative and qualitative data. With regard to the first question on increasing usability, an increase in the SUS score could be considered a technically meaningful measure. Furthermore, changes in the TUI-ITU scale reflect changes in intended use, which is a logical preliminary stage for actual use of the intervention. Finally, at the societal level, the study’s results will help explain the influence of DFree on reducing the workload of nurses and encourage nurses to use the DAT in nursing care as an additional resource for better outcomes in bladder dysfunction interventions.

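### The Discussion uses an increase in the SUS score to answer the usability question, but the only stated SUS administration is at the end of the trial, so no SUS change can be estimated

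*Protocol article*

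**What the plan says.** Methods, Quantitative Evaluation, describes the SUS as a 10-item scale scored from 0 to 100, gives its reference value ("Systems are considered fit if they achieve a benchmark of 68"), and grades scores with the adjective scale in Table 4. After Table 3 it fixes the timing: "The measurement time T1 of the SUS was parallel to the measurement time T3 of the TUI at the end of the trial". Table 2 defines that occasion as "T3: Behavior—end of technology testing". Table 2 lists TUI versions and scales only and has no SUS entry at T1, T2 or T3.

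The Discussion then states: "With regard to the first question on increasing usability, an increase in the SUS score could be considered a technically meaningful measure". It also says that the study has no control group.

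Results states: "Additionally, a change in the perceived usability of the DFree app among nurses is expected". That sentence does not name an instrument.

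**The concern.** An increase needs an earlier value, and the article gives none for these nurses. The Discussion therefore relies on a quantity that the stated schedule does not produce. This is not a detail that a condensed article leaves to a fuller document, because the article itself gives both the SUS timing and a measure which that timing rules out.

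At stake is what the trial can say about usability from its dedicated usability instrument. A final score against 68 shows whether the nurses rate the device acceptably after the trial period. It does not show whether their rating moved. A first rating that was not collected cannot be recovered once the nurses have used the device for three months.

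**Working it through.** No sample size, power or error-rate figure is involved. The check counts measurement occasions and sets the passages side by side.

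**Inputs**
- SUS occasions stated: 1, at TUI T3 (Methods, Quantitative Evaluation, after Table 3).
- Control group: none (Discussion).
- Earlier SUS value for these nurses: none given.
- Sample: up to 45 nurses (Methods, Quantitative Evaluation).
- TUI BEN: planned at T2 and T3 (Table 2).

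**Step 1: SUS change scores.** With k occasions, each nurse gives k − 1 successive differences. For the SUS, k = 1, so k − 1 = 0 per nurse and 45 × 0 = 0 overall. Without a control group, no between-group contrast can stand in for the missing first value.

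**Step 2: what the final score says about change.** Take an end score of 75 as an illustration. Table 4 grades it as good. The SUS runs from 0 to 100, so the unknown earlier score could lie anywhere in that range. The change could then lie anywhere from 75 − 100 = −25 to 75 − 0 = +75. The grade is the same whether usability rose, fell or stayed flat. The benchmark and the adjective scale describe a level, and neither is a baseline for these nurses.

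**Step 3: what can be estimated as a change.** For BEN, Table 2 gives k = 2, so there is k − 1 = 1 paired difference per nurse who completes both questionnaires. Table 1 defines BEN as perceived user-friendliness, and Results labels the same scale usability.

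**Side by side**

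| Statement | Needs | Stated design provides |
|---|---|---|
| Discussion: increase in SUS score | 2 SUS occasions | 1 |
| Results: change in perceived usability, if read as SUS | 2 SUS occasions | 1 |
| Results: change in perceived usability, if read as BEN | 2 BEN occasions | 2 (T2, T3) |
| Abstract: high usability rating expected | 1 SUS occasion and a reference | 1, with 68 and Table 4 |

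Only the first row is a definite contradiction. The Results sentence contradicts the schedule only on one of its two readings.

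**The case against.** The strongest reply is that little depends on this sentence. The Abstract makes the TUI results the primary target values. The objectives at the end of the Introduction concern support for continence care, intention to use and nurses' reception, and none mentions a change in SUS. The Abstract expects a high usability rating, which is a level, and one end-of-trial SUS can deliver that. The SUS increase appears in a single conditional sentence in the Discussion of an exploratory study. All of this stands, and it limits the weight of the point. It does not remove the contradiction: the conditional wording concerns whether an increase would be meaningful, not whether one can be calculated.

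A second reply is that the label T1 for the SUS suggests a series, so a later SUS may be set out elsewhere. The article defines no SUS T2, and a T1 at the end of the trial leaves no room for a second SUS within it.

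A third reply concerns adding an early SUS. Nurses who have barely used the device would be rating first impressions, and without a control group a later rise would mix learning with the usability of the device. Both cautions stand and must accompany any such change score.

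A reader might go further and infer that no change in usability can be measured at all, or that the change expected in Results must be a SUS change. The documents do not support either. BEN is repeated, and the Results sentence does not name the SUS. Methods does describe the SUS as subjectively perceived usability, so that sentence is ambiguous. Nor do the documents support calling the SUS change a declared outcome that the trial will fail to deliver.

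**Conclusion.** The point holds for the SUS. With one stated occasion and no control group, the increase named in the Discussion cannot be estimated for any of up to 45 nurses. The SUS can support only an end-of-trial level, judged against 68 and the adjective scale. A change in perceived user-friendliness remains estimable from BEN between T2 and T3, and the Results sentence may mean exactly that.

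The conclusion rests on the article's own schedule being complete for the trial period. It needs no assumption about the SD or the sample size. It affects neither the primary TUI results nor any decision rule. It is still worth correcting, because it determines whether the trial can report a SUS change or only a SUS level, and the correction costs little.

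**What to change.** Choose one of two routes.

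**Route A: add an early SUS.** Give the 10-item SUS to the same nurses at an early occasion once they have actually handled the device, for example with the TUI at T2. First settle what T2 is: the Quantitative Evaluation text makes it the first presentation of the prototype, whereas Table 2 makes it testing. If it is only the presentation, place the form after first handling. Report the paired within-nurse SUS change with a 95% CI. State that early ratings reflect limited exposure and that an uncontrolled change mixes learning with usability. The cost is one 10-item form per nurse (at most 45 × 10 = 450 item responses), an amendment sentence and the clarification of T2.

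**Route B: keep one SUS and change the text.** In the Discussion, replace the SUS-increase statement with a comparison of the end-of-trial mean SUS, with its 95% CI, against 68. In Results, state that the expected usability change is assessed with TUI BEN from T2 to T3. This needs no extra data collection. The price is that the trial makes no statement about change in the SUS.

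Under Route A too, the Results sentence should name its instrument.

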**Acceptable**		
	90-100	Outstanding: best imaginable
	80-89	Excellent
	68-79	Good
**Marginal**		
	50-67	So-so
**Not acceptable**		
	35-49	Mad
	0-34	Very bad: not imaginable

### Qualitative Evaluation

The number of nursing staff members who participate in the expert interviews [52] is limited to 6 to 10 nurses. The selection follows the principles of theoretical sampling, and the aim of the surveys is not to achieve statistical representativeness [53]. Using guided interviews, the survey will be conducted with the clear aim of obtaining specific knowledge that is necessary to answer the precise (and theoretically embedded) research question. The interviews conducted after the completion of the empirical research program on the DFree Professional are useful for obtaining either supply-relevant and “practical” background knowledge or information on the practical implementation of the ultrasonic sensor [52]. The methodological preparation was based on the mechanism-exploring research paradigm of qualitative content analysis that was described by Gläser and Laudel [54], who suggested a 5-step approach commencing with the development of the interview guide and ending by logging the respective surveys [52,54]. Herein, individual steps may be simultaneously taken in parallel to optimize the overall processing time for data collection. The sets of questions fixed in the guidelines were based on preliminary considerations and were developed into a complete guide after the interviews in the first submission (Multimedia Appendix 1).

The methodological recourse to guided interviews for data collection originated from the fact that conducting expert interviews requires good knowledge of the field of investigation [14]. However, challenging hurdles to field access exist within the framework of the DFree study and include the implementation of the DAT and its components in the ecosystem of a clinical ward during normal operational business hours. For example, Adner and Kapoor [55,56] argue that the impact of external challenges through innovation depends not only on their magnitude but also on their position in the respective ecosystem. This implies that the physical functionality of the technology during regular operations in the clinical ward ecosystem is of fundamental importance for assessing the technology itself. Overcoming these hurdles ensures that the surveys of nursing staff on their experiences using DFree Professional within the framework of the nursing process are actually theory-based and methodologically reflected. In the expert interviews, narrative elements relate to the perception of free fitting to problems in continence care from the perspective of nurses are a key focus area [57,58]. The interview guidelines have been developed iteratively using SPSS Statistics 25 [59]. At the end of the 3-month trial period, face-to-face interviews will be conducted using the Phillips Voice Tracer device. All interviews will be transcribed and analyzed based on the content analysis method [54] supported by Microsoft Excel 2016 (Microsoft Corporation) to process data.

All nursing professionals in this study will be recruited through contact with the University Clinic Halle (Saale) and will include those who are employed in clinics for neurology, neurosurgery, and geriatrics. The staff council was informed in advance, and approval of the project was requested.

### Ethics Approval

All procedures involving human participants or human tissue will be performed in accordance with the institutional and national research committee ethical standards and tenets of the 1975 Declaration of Helsinki and its later amendments or comparable ethical standards. Informed consent will be obtained from all the participants. This study was approved by the Ethics Committee of the Faculty of Medicine, Martin-Luther-University Halle-Wittenberg (approval no. 2023–031, dated May 9, 2023). The study was registered in the German Register of Clinical Studies (registration no. DRKS00031483), and the protocol has not been published previously.

## Results

Data collection would begin in the summer of 2023, and the initial results are expected in the winter of 2023. This study will evaluate the implementation of DFree to support nurses in reducing their workload pertaining to continence care. A change in ITU (TUI Scale) is expected. To investigate the possible causes for the measured change, 7 additional characteristics—curiosity (NEU), anxiety about technology, interest (INT), usability (BEN), usefulness (NÜT), skepticism (SKE), and accessibility (ZUG)—will be evaluated 3 times. Furthermore, this study will generate structured feedback that can support developers in further improving DAT DFree. Consequently, a reduction in the number of unsuccessful toilet visits or uncontrolled micturition events while wearing DFree will be recorded and documented by nurses through numerical counting. This will show whether the use of DFree is a practical and advantageous measure for mitigating the nurses’ workload in the context of continence care. As nurses are often poorly equipped to respond to such DAT implementation, the results should serve as a guideline for further improvement of DFree. The combination of qualitative and quantitative instruments addresses the additional aspects that nursing staff would have in mind but will not be assessed using only a quantitative instrument (TUI). Additionally, a change in the perceived usability of the DFree app among nurses is expected.

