**Results:**

It is expected that the intention to use will be confirmed by nurses, and the number of nursing problems, such as bladder dysfunction-induced bedwetting, will be reduced with a high rating of DAT usability.

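### An event count taken only while DFree is worn, with no off-device count described, cannot identify a reduction or settle the workload question

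*Protocol article*

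**What the plan says.** The relevant text is in the Results section of the protocol article, which sets out what the study will deliver. It says that "a reduction in the number of unsuccessful toilet visits or uncontrolled micturition events while wearing DFree will be recorded". The method is a plain count kept by the nursing staff. The next sentence draws the inference: "This will show whether the use of DFree is a practical and advantageous measure for mitigating the nurses’ workload". The Results paragraph of the Abstract states the matching expectation, that "the number of nursing problems, such as bladder dysfunction-induced bedwetting, will be reduced".

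The Discussion lists among the limitations that "no control group has been included in this study", and also that the bladder dysfunctions are mixed, covering both incontinence and retention.

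The only measurement described before the device is introduced is T1 (Quantitative Evaluation and Table 2), a questionnaire to nurses on curiosity and fear of technology. It contains no patient events. According to the Methods paragraph of the Abstract, the primary target values are the TUI results, analysed descriptively.

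**The concern.** A reduction is a difference or ratio between two rates. The stated counting window supplies one of them, the events during wear. The article describes nothing to set against it: no earlier period, no non-wear days and no parallel group. Yet the text says that the count will answer the workload question.

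There is a second gap between count and conclusion. Nursing workload is more than the number of failed toilet visits and wetting episodes. The Technical Description says that the device notifies nurses and triggers an alarm at a set threshold, so it creates tasks as well as possibly removing some. A real fall in events would still not show that net work had fallen.

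Relief of workload is part of the stated rationale (Objective and Conclusions in the Abstract, Introduction, Discussion), and the Discussion offers the results as a basis for effect assessment in later studies. A during-wear count reported as a reduction could therefore mislead the planning of the next trial.

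**Working it through.** **1. The design figure that can be reproduced.** The article gives up to 45 nurses, as 15 in each of three clinical units: 3 × 15 = 45. This agrees, but it concerns nurses and questionnaires. No number of patients, events or wearing days is given, so the article has no figure for the event count that could be recomputed.

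**2. What the claim requires.**

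Percent change = 100 × [(events during wear ÷ wearing days) ÷ comparison rate − 1]

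- Events during wear: will be counted (Results).
- Wearing days: not stated in the article.
- Comparison rate in the same or similar patients without the device: no source is described. T1 is a nurse questionnaire, and there is no control group.

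**3. How much the missing quantities matter.** All figures in this step are assumptions for illustration. Take 60 events during wear.

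- 50 wearing days: 60 ÷ 50 = 1.2 per day
- 100 wearing days: 60 ÷ 100 = 0.6 per day
- 200 wearing days: 60 ÷ 200 = 0.3 per day

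Percent change against an unobserved comparison rate:

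| Rate during wear | 0.3/day | 0.6/day | 0.9/day | 1.2/day |
|---|---|---|---|---|
| 1.2 (50 days) | +300% | +100% | +33% | 0% |
| 0.6 (100 days) | +100% | 0% | −33% | −50% |
| 0.3 (200 days) | 0% | −50% | −67% | −75% |

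For example, 0.6 ÷ 0.3 − 1 = +100% and 0.6 ÷ 1.2 − 1 = −50%.

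If wearing days are properly recorded, the analysis sits on a single row. On the middle row the answer still runs from a doubling to a halving. The missing comparison rate is therefore enough by itself to leave the direction open; the exposure unit only widens the range.

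**4. Could a trend within wearing time serve instead?** Early and late wear could be compared descriptively. That would not isolate the device: nurses choose DFree for willing patients, the patients observed will change over the 90 days, and two kinds of dysfunction are pooled.

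**5. From events to workload.** The other quantitative instruments are the TUI and the System Usability Scale, which measure acceptance and perceived usability. The article describes no count of device handling or alarm responses and no measure of nursing time. Net workload therefore cannot be derived from the event count, even with a comparator.

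**The case against.** The strongest reply is that this is a condensed article about an exploratory, nonrandomized feasibility study, and the count appears in one sentence on expected results. The word reduction implies some reference, and the reference period, recording form and exposure unit may be set out in a fuller protocol. This stands for the exposure unit: a reader might infer that the study has no denominator, but silence in an article does not establish that. It carries less weight for the comparator. The article fixes the counting window as the time of wear, rules out a control group, and describes its pre-device measurement without any event count.

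Second, the absence of a control group and the mix of incontinence and retention are openly listed as limitations. That is correct, and neither is a concealed fault. But the disclosure does not support the sentence saying that the count will answer the workload question.

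Third, burden on nurses is not ignored. The TUI covers usefulness, user-friendliness and skepticism, and the interviews cover experience of using the device. These capture perceived burden. They cannot supply a numerical reduction.

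A reader might also infer that the plan leads to a favourable conclusion whatever the data show. The text does not support this: it asks whether the device helps, and no decision rule turns a count into a verdict. The result would be uninterpretable, not predetermined.

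**Conclusion.** The concern holds for this outcome and the inference attached to it. As described, a count during wear with no off-device count and no control group identifies neither the sign nor the size of a reduction, and an event count alone does not measure net workload. In the illustration, the same 60 events fit anything from +300% to −75%, or from +100% to −50% once wearing time is fixed at 100 days. Those figures are assumed; they show that the effect is not identified and do not size an error in the article.

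The conclusion rests on reading the article as complete about when events are counted. If a fuller protocol specifies a pre-device or off-device count, the point reduces to one of wording.

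It would be a mistake to infer that the study's main result is compromised. The primary target is the TUI, and neither its descriptive analysis nor the number of nurses depends on this count.

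**What to change.** Preferred: have nurses make the same count, with the same event definitions, in the same consenting patients before first wear, on non-wear days that occur anyway, or both. Record exposure time in each state. Report descriptive event rates per patient-day with and without DFree, separately by dysfunction type where numbers allow. This should be settled before a patient first wears the device, because a pre-wear count cannot be recovered afterwards. Even then, the workload statement should not rest on the event count alone.

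The cost is extra recording by ward staff. The contrast would remain before-after and not randomised, and the baseline may be short in inpatients whose condition is changing, so it should be reported as descriptive.

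Alternative, if no off-device count is taken: in the Results section, replace the promise of a reduction, and the sentence saying that the count will show whether workload is mitigated, with a description of event rates during wear. Draw no workload conclusion from the count. Perceived workload can still be reported from the interviews. This costs only wording.
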